### Tobacco use

We hypothesize subjects in the mDOT arm will have greater CO-verified, 7-day point prevalence abstinence throughout the intervention period; reductions in cigarettes/day and Fagerström Test for Nicotine Dependence scores; and ≥ 24-hour quit attempts compared to subjects receiving self-administered varenicline. We will compare the proportion of participants who achieve CO-verified tobacco abstinence at all follow-up timepoints in the two study arms using mixed-effects models. In addition, we will compare secondary tobacco use outcomes between study arms using chi-square or Wilcoxon rank sum tests, and explore differences in CO-verified abstinence at 24 weeks using Fisher exact tests. All analyses will use an intent-to-treat approach. In addition, we will apply mixed effects models to test the significance of varenicline adherence on smoking cessation across the post-baseline assessment time points.

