**Study measures**								
Sociodemographic characteristics	X							
Tobacco use behavior, FTND^a^	X			X	X	X	X	X
Smoking endpoints^b^				X	X	X	X	X
Medication adherence		X	X	X	X	X	X	
Mini-International Neuropsych. Interview	X			X	X	X	X	X
Modified scale for suicidal ideation	X			X	X	X	X	
Brief symptom Inventory	X			X	X	X	X	X
Medication adverse events		X	X	X	X	X	X	
Alcohol and other drug use	X			X	X	X	X	X
Urine toxicology tests	X			X	X		X	
Medication adverse events		X	X	X	X	X	X	

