**Subject reimbursement**								
$ Amount^c^	$15	$10	$10	$15	$15	$15	$15	$15

^a^Fagerström Test for Nicotine Dependence.

^b^Carbon monoxide-verified abstinence, number of cigarettes smoked per day, Fagerström Test for Nicotine Dependence score, quit attempts lasting ≥ 24 hours.

^c^To ensure pill count completion, TAU subjects will be given partial reimbursement ($5-$10 dollars per visit) for research assessments and $5 for completion of pill counts at each follow-up visit during the intervention period.

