### Tobacco use measures

Our primary tobacco use outcome is biochemically validated 7-day point prevalence abstinence at each follow-up visit, with abstinence defined as including both self-reported smoking abstinence and carbon monoxide (CO) < 8 p.p.m. (Micro Smokerlyzer®, Bedfont Scientific) [40]. Self-reported tobacco abstinence will be measured at all visits by asking participants, “Have you smoked at least part of a cigarette in the past 7 days, even a puff?” Our secondary tobacco outcome measures include: 1) number of cigarettes smoked per day; 2) Fagerström Test for Nicotine Dependence score; 3) quit attempts lasting ≥ 24 hours; and 4) durability, measured by CO-verified tobacco abstinence at week 24.

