### Varenicline adherence

We hypothesize that adherence in the mDOT arm will be higher than in the TAU arm throughout the intervention period. We will apply a mixed effects linear model to test the significance of the mDOT effect on the repeatedly measured pill count adherence outcome at weeks 1, 2, 3, 6, 9, and 12. This model accounts for within-subject longitudinal outcome correlation by taking the subject-level intercept as random, and it is robust in the context of missing data. The model will also include variables not equally distributed between the study arms at baseline, as well as psychiatric symptoms and substance abuse. All analyses will use an intent-to-treat approach.

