### Sample size and power considerations

Among methadone-maintained smokers receiving a nicotine patch in a clinical trial, overall adherence over 90 days was 44.1 percent [12]. Assuming a 13-percent difference in adherence between the DOT and TAU groups as seen in weeks 2–12 of a methadone clinic-based antiretroviral DOT trial [30], the hypothesized adherence effect would be 57 percent in the mDOT arm and 44 percent in the TAU arm. We estimate sample sizes N per group required to detect this effect at a two-sided α = 0.05 as N per group = 11, 14, and 17 for intraclass correlation (ICC) = 0.1, 0.2, and 0.3, respectively.

Given that the efficacy of NRT and bupropion in methadone maintenance patients has been half of that observed in clinical trials of these medications in the general population [7,8,15], we estimate that abstinence rates at 12 weeks in the TAU varenicline arm would be 22 percent. We estimate that increased adherence would double the odds of cessation [13,17,18,46], and thus the abstinence rates at 12 weeks in the DOT arm would be 44 percent. We estimate sample sizes required to detect the hypothesized intervention effect (22% and 44% on a binary scale) at a two-sided alpha = 0.05 as N per group = 29, 33, 38 for within-subject ICC = 0.1, 0.2, and 0.3, respectively. Estimating an approximately 25 percent attrition rate at 12 weeks, we plan to recruit 100 participants.

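### Cigarettes per day and FTND score are compared with a two-sample rank test that is valid but leaves their baseline and repeated measurements largely unused

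*Protocol article*

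**What the plan says.** The Tobacco use measures section lists the secondary tobacco outcomes as "1) number of cigarettes smoked per day; 2) Fagerström Test for Nicotine Dependence score; 3) quit attempts lasting ≥ 24 hours", followed by abstinence at week 24. The Tobacco use analysis section hypothesises "reductions in cigarettes/day and Fagerström Test for Nicotine Dependence scores" in favour of the mDOT arm, and then states "we will compare secondary tobacco use outcomes between study arms using chi-square or Wilcoxon rank sum tests". It names no visit, covariate or repeated-measures model for these comparisons. Week-24 abstinence has its own Fisher exact test.

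Table 1 marks tobacco use behavior and FTND at baseline and at weeks 3, 6, 9, 12 and 24. Its smoking endpoints row is marked at the same five follow-ups, and the footnote defines that row as "Carbon monoxide-verified abstinence, number of cigarettes smoked per day, Fagerström Test for Nicotine Dependence score, quit attempts lasting ≥ 24 hours".

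Elsewhere the plan works longitudinally. It compares "CO-verified tobacco abstinence at all follow-up timepoints in the two study arms using mixed-effects models". For pill-count adherence it chooses a linear mixed model and gives the reason: "This model accounts for within-subject longitudinal outcome correlation by taking the subject-level intercept as random". The Randomization section stratifies by clinical site and HIV status.

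**The concern.** A reduction is a statement relative to baseline, and the trial collects a baseline and five follow-up values for each outcome. A two-sample rank test uses at most one summary value per person. It does not adjust for where that person started or for the stratification factors. The reasons the plan gives for modelling adherence longitudinally apply equally here, and it offers none for treating these two outcomes differently.

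This could matter more than is usual for secondary outcomes. The Discussion reports abstinence of 10.5% and 4% in two varenicline trials in this population, against the 22% and 44% used for planning, and concedes that smaller abstinence effects may be missed. It then justifies the trial partly as a source of effect-size estimates for later studies. If abstinence is that rare, the graded smoking measures may carry much of the remaining information on smoking. An adjusted difference with a confidence interval serves effect-size estimation better than a rank-test p-value.

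**Working it through.** **The plan's own figures.** The article gives no sample size or power for cigarettes per day or FTND. Its abstinence calculation reads "at a two-sided alpha = 0.05 as N per group = 29, 33, 38 for within-subject ICC = 0.1, 0.2, and 0.3". Power and the number of repeated measurements m are not stated. With 80% power, pooled variance and no continuity correction, 22% against 44% needs 71 per arm for a single measurement. Multiplying by (1 + (m − 1) × ICC)/m with m = 3:

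- ICC 0.1: 71 × 1.2/3 = 28.4
- ICC 0.2: 71 × 1.4/3 = 33.1
- ICC 0.3: 71 × 1.6/3 = 37.9

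These match the stated 29, 33 and 38 to within one. On this reconstruction, the plan already relies on repeated measurements to bring 71 per arm down to 29–38 for abstinence. The planned tests for cigarettes per day and FTND take no such credit.

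**Inputs for the two outcomes.** About 25% attrition from 100 leaves 75, or 37.5 per arm; 37 is used. The following are assumptions that are not in the document: correlation r of 0.4 to 0.7, equal between baseline and each on-treatment visit and among those visits; normal data; equal variances; an effect that is constant over weeks 3 to 12.

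**Variance relative to one raw follow-up value (set to 1).**

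- Change from baseline: 2(1 − r)
- One visit, baseline-adjusted: 1 − r²
- Baseline-adjusted against change: (1 − r²)/(2(1 − r)) = (1 + r)/2
- Mean of weeks 3, 6, 9 and 12, baseline-adjusted: (1 + 3r)/4 − r²

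| r | Adjusted vs raw, 1 − r² (cut) | Adjusted vs change, (1 + r)/2 (cut) | Adjusted mean of four visits |
|---|---|---|---|
| 0.4 | 0.84 (16%) | 0.70 (30%) | 0.390 |
| 0.5 | 0.75 (25%) | 0.75 (25%) | 0.375 |
| 0.6 | 0.64 (36%) | 0.80 (20%) | 0.340 |
| 0.7 | 0.51 (49%) | 0.85 (15%) | 0.285 |

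In sample-size terms, baseline adjustment alone is worth 1/0.84 = 1.2 to 1/0.51 = 2.0 times the participants against raw values, and 1/0.70 = 1.4 to 1/0.85 = 1.2 times against change scores.

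**Illustrative power** for a 0.5 SD effect at 37 per arm, two-sided 5%. The Wilcoxon variance is multiplied by π/3 = 1.047, its efficiency loss under normality.

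| r | Wilcoxon, one visit | Wilcoxon, change | Adjusted, one visit | Adjusted, weeks 3–12 |
|---|---|---|---|---|
| 0.4 | 56% | 48% | 65% | 93% |
| 0.5 | 56% | 56% | 70% | 94% |
| 0.6 | 56% | 65% | 77% | 96% |
| 0.7 | 56% | 77% | 85% | 98% |

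Worked example, Wilcoxon at one visit: SE = √(2/37 × 1.047) = 0.238; 0.5/0.238 − 1.96 = 0.14; power 56%. The difference detectable with 80% power is (1.96 + 0.84) × 0.238 = 0.67 SD. For the adjusted analysis over weeks 3–12 at r = 0.5 it is (1.96 + 0.84) × √(2/37 × 0.375) = 0.40 SD.

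Simulation with 2000 runs at r = 0.3, 0.5 and 0.7 gave 52–55% power for the single-visit Wilcoxon and 91–97% for the adjusted longitudinal analysis. Type I error was 4.2–6.0% across methods.

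**The case against.** The strongest reply is that nothing here is an error. Wilcoxon and chi-square are valid two-arm tests, these are secondary outcomes of a self-described pilot, and the primary adherence and abstinence outcomes already have mixed models. A rank test is also a defensible choice for skewed counts, and abstainers contribute zero cigarettes, so a plain log scale would fail. All of this stands. It limits the severity and shapes the fix, but does not recover the lost precision.

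Secondly, a condensed article may leave visits, covariates and missing-data rules to the full plan. That is fair for those details. The choice of test, however, is stated, and it is the choice of test that loses precision.

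Thirdly, the word reductions may mean that Wilcoxon is applied to change from baseline. The text does not say. On that reading baseline is used, and the gain from adjustment is the smaller 30 to 15%, but a gain remains at every r below 1.

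A reader might go further and infer separate tests at every visit: three outcomes at five visits make 15 p-values, with a chance of 1 − 0.95^15 = 54% of at least one false positive if independent. The document does not support this. It names no visit for these tests, a single end-of-treatment comparison fits the wording equally well, and repeated visits on the same people are not independent. Nor does it say that participants missing at a visit are excluded; it states only an intent-to-treat approach.

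**Conclusion.** The point holds as a loss of precision, not of validity. Baseline adjustment would cut variance by 16 to 49% if Wilcoxon is applied to raw follow-up values, or by 30 to 15% if applied to change scores, for an assumed correlation of 0.4 to 0.7. Using the four on-treatment visits together would cut it further.

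The power figures are illustrative. They rest on a 0.5 SD constant effect, normality, equal correlations and 37 per arm with complete visits. The gain from repeated visits shrinks if the effect is confined to one visit, or if follow-up values correlate more strongly with each other than with baseline. Baseline cigarettes per day is read from the tobacco use behavior row of Table 1, since the smoking endpoints row has no baseline mark. Chi-square is taken to serve the quit-attempt outcome. Severity is modest.

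**What to change.** Replace the Wilcoxon comparison of these two outcomes as follows:

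- **FTND score:** linear mixed model over weeks 3, 6, 9 and 12.
- **Cigarettes per day:** a method that accommodates zeros over the same visits, such as a negative binomial mixed model or GEE, or a rank-based ANCOVA.
- **Terms in both:** arm, visit, arm × visit, baseline value, site and HIV status.
- **Reporting:** one pre-specified on-treatment contrast per outcome with a confidence interval. Treat week 24 as a separate contrast and keep Wilcoxon as a sensitivity analysis, stating whether it uses raw values or change and at which visit.

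The cost is analysis wording, slightly more analysis work and reliance on a model assumption. No visit, measurement or participant is added.

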### Moderating effects of drug use and psychiatric symptoms

We hypothesize that ongoing drug use and psychiatric symptoms will negatively moderate adherence effects. The dependent variable will be varenicline adherence. Potential moderating variables include cocaine, heroin, benzodiazepine, or marijuana use (defined as a binary variable based on either self-reported use or positive urine toxicology result); hazardous alcohol use (defined as AUDIT score ≥ 8 for men and ≥ 4 for women); incident major depressive, manic, or psychotic episodes; suicidal ideation with plan or intent; and symptoms of psychologic distress (BSI Global Severity Index T score ≥ 63). We will test moderators using a treatment group x moderating variable interaction term, and set an alpha significance level of 0.15 for interaction analyses.

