### Participants

Our goal is to enroll subjects representative of methadone-maintained smokers, while considering varenicline precautions. Eligible persons are: 18 years or older; smoking 5 or more cigarettes per day; interested in quitting smoking with a plan to quit in ≤ 6 months (ladder of change score 6–8); enrolled in methadone treatment for at least 3 months, receiving methadone in the clinic 3, 4, 5, or 6 times per week, without three or more clinic absences in the prior 2 weeks; English-speaking; able to provide informed consent; not pregnant, breastfeeding, or trying to conceive; and have not taken varenicline in the past 30 days. Unstable liver, cardiac, pulmonary, renal, or infectious diseases are exclusionary. Psychiatric exclusion criteria include current major depressive or manic episode, current psychotic disorder, past-year suicide attempt or psychiatric hospitalization, or current suicidal ideation with plan or intent.

Subjects will be recruited by research assistants in methadone clinic waiting areas, as well as by word-of-mouth, posted fliers, and clinic counseling and medical staff referral. All subjects will sign written informed consent. We will conduct a brief screening interview, then abstract laboratory and treatment data from clinic charts to further assess eligibility. Eligibility will be confirmed only after the study physician completes a clinical and structured psychiatric interview using the Mini-International Neuropsychiatric Interview 6.0.0 (M.I.N.I.) and Columbia Suicide Severity Rating Scale, and conducts a physical examination and urine pregnancy test (if applicable). Interviews will be completed in private offices in the methadone clinics.

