#### Addressing varenicline risk potential

Case reports of behavior change, agitation, depression, and suicidality among patients taking varenicline led to an FDA boxed warning in 2009 [47]. Despite a growing body of research demonstrating the safety of varenicline among patients with mental illness and substance use disorders [48-56], we will take multiple precautions to address varenicline’s psychiatric risk potential.

Prior to enrollment, information regarding potential psychiatric risks will be discussed with subjects during the informed consent process. During screening, a physician will assess potential subjects for current psychiatric illness or suicidal ideation using structured instruments. Individuals with psychiatric symptoms not receiving psychiatric care will be referred to a mental health center.

Subjects will be assessed for incident psychiatric symptoms throughout the intervention period. At brief visits (weeks 1 and 2), and weeks 3, 6, 9 and 12, the interviewer will ask open-ended questions about symptoms that have emerged or increased in intensity since the prior visit. At week 3, 6, 9, and 12 follow-up visits, psychiatric symptoms will be assessed via structured instruments. Prior to concluding the research visit, the research assistant will review flags programmed into the computerized survey record for symptoms consistent with incident major depressive or manic episode, psychotic disorder, or suicidal ideation and will refer subjects to outpatient or emergency treatment according to detailed study protocols.

If subjects meet criteria for current major depressive or manic episode, psychotic disorder, or suicidal ideation with plan or intent, varenicline will be discontinued. To facilitate medication discontinuation among TAU group subjects who fill varenicline prescriptions at community pharmacies of their choosing, prescriptions will not be given directly to study subjects; rather, the study physician will call in all prescriptions and track the pharmacies used. If DOT group subjects meet criteria for medication discontinuation, the study physician will notify the study pharmacy and the methadone clinic nurses.

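### Incident psychiatric episodes and suicidal ideation are tested as moderators of varenicline adherence, although by protocol they arise only after enrolment and stop varenicline

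*Protocol article*

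**What the plan says.** All references are to the protocol article.

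- *Moderating effects of drug use and psychiatric symptoms*: "The dependent variable will be varenicline adherence". The hypothesis is that ongoing drug use and psychiatric symptoms moderate adherence effects negatively. Besides drug use and hazardous alcohol use, the moderators are "incident major depressive, manic, or psychotic episodes; suicidal ideation with plan or intent; and symptoms of psychologic distress". On method: "We will test moderators using a treatment group x moderating variable interaction term", and the authors will "set an alpha significance level of 0.15 for interaction analyses".
- *Participants*: the psychiatric exclusions are "current major depressive or manic episode, current psychotic disorder, past-year suicide attempt or psychiatric hospitalization, or current suicidal ideation with plan or intent".
- *Potential moderating variables: psychologic symptoms*: incident symptoms are assessed at weeks 3, 6, 9 and 12.
- *Addressing varenicline risk potential*: "If subjects meet criteria for current major depressive or manic episode, psychotic disorder, or suicidal ideation with plan or intent, varenicline will be discontinued".
- *Adherence measures*: medication taken over the 12-week course is expressed relative to the target dose. *Varenicline adherence* models pill-count adherence at weeks 1, 2, 3, 6, 9 and 12, by intention to treat.
- No section says how doses due after a protocol-required stop are scored.
- Testing for moderation is a declared aim (*Background*; opening of *Methods/Design*).

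**The concern.** A moderator should be a characteristic that treatment cannot change and that does not itself set the outcome. The incident episodes and suicidal ideation fail on both counts. Nobody has them at entry, so they exist only as events during follow-up. When they occur, varenicline stops in either arm, and adherence measured against the full course must fall.

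Once dosing has stopped, the two arms cannot differ in later doses. The arm difference among people with an event is therefore compressed towards zero, which in an interaction test looks like a weaker mDOT effect in people with psychiatric symptoms. The protocol hypothesises exactly that pattern, so the artefact would read as confirmation. A larger sample would not remove it.

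**Working it through.** **Inputs**

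- Dosing (*Interventions*): once daily for 3 days, twice daily for 4 days, then twice daily for 11 weeks.
- Planning adherence (*Sample size and power considerations*): 57% mDOT and 44% TAU, a difference of 13 points.
- Assumptions: one tablet per dose; stopping occurs at an assessment week; before the stop, participants take doses at the planning rates; doses after the stop stay in the target and count as not taken.

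**Target tablets.** 3×1 + 4×2 + 77×2 = 3 + 8 + 154 = 165. Tablets due by week *w* = 11 + 14(*w* − 1).

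**Cumulative scoring.** The fraction of the target due by the stop is *f* = due/165. The arm difference becomes 13*f*, and the apparent interaction is 13*f* − 13.

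| Stop | Due | *f* | TAU | mDOT | Difference | Apparent interaction |
|---|---|---|---|---|---|---|
| Week 3 | 39 | 23.6% | 10.4% | 13.5% | 3.1 | −9.9 |
| Week 6 | 81 | 49.1% | 21.6% | 28.0% | 6.4 | −6.6 |
| Week 9 | 123 | 74.5% | 32.8% | 42.5% | 9.7 | −3.3 |

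**Visit-by-visit scoring.** Suppose each of the six visits scores its own interval and intervals after the stop score zero. A stop at week 3, 6 or 9 then leaves 3, 4 or 5 of 6 visits unaffected. The visit-averaged difference is 13×3/6 = 6.5, 13×4/6 = 8.7 or 13×5/6 = 10.8 points, so the apparent interaction is −6.5, −4.3 or −2.2. It is smaller, with the same sign.

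**Post-stop doses treated as missing.** The arithmetic cap goes. The interaction then either has almost no adherence data after the event or classifies earlier adherence by a later event. Neither is effect moderation.

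**Does the test reject too often?** A simulation used 100 participants 1:1, an assumed SD of 20 points, no true moderation, events unrelated to arm or adherence, stops equally likely at week 3, 6 or 9, and adherence scaled by *w*/12.

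| Event rate | Mean interaction, stopping | Rejection at 0.15, stopping | Rejection at 0.15, no stopping |
|---|---|---|---|
| 5% | −6.2 | 0.09 | 0.14 |
| 10% | −6.7 | 0.13 | 0.14 |
| 20% | −6.4 | 0.19 | 0.15 |
| 30% | −6.4 | 0.24 | 0.16 |

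Without stopping, the mean interaction stays within about half a point of zero. The bias is present at every event rate; rejections above nominal appear only at the higher rates.

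**Sparse cells.** With *e* events split evenly between arms, SE = SD × √[2/(*e*/2) + 2/((100 − *e*)/2)]. For *e* = 10 and SD 20: 20 × √(0.400 + 0.044) = 13.3 points, as large as the planned effect. Over 2 to 10 events and an assumed SD of 20 to 30, power to detect a true 13-point interaction at 0.15 is about 17% to 33%.

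**Number of tests.** The fewest is 5 (any drug, alcohol, any episode, suicidal ideation, BSI). The most is 10 (4 drugs, alcohol, 3 episode types, suicidal ideation, BSI). The stopping rule covers 2 of 5, or 4 of 10. The chance of at least one false positive at 0.15 each, if independent, is 1 − 0.85^5 = 56% to 1 − 0.85^10 = 80%.

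**The case against.** - **Scope.** A reader might infer that the whole moderator analysis is tied to the stopping rule, because BSI distress sits in the same list. The documents do not support that. BSI distress, drug use and alcohol use are neither entry exclusions nor grounds for stopping. This objection stands.
- **Timing of the other moderators.** No time point is fixed for them in the moderator section, and all have baseline measurements, so the SAP could select baseline. That stands in part: the wording about ongoing use and the schedule at weeks 3 to 12 point to follow-up values, but do not settle it.
- **Size.** The 23.6% and 49.1% ceilings apply in both arms, so they describe the effect of having an event and are not themselves the interaction bias. The bias depends on a scoring rule that a SAP would normally give. That stands for the size. No scoring rule turns an event that arises after enrolment and ends treatment into a valid moderator.
- **Detection by arm.** One might suspect more events are found under mDOT because nurses there use a side-effect script. No section says the script feeds the moderator data, and the structured assessments are scheduled for all participants, so this is speculation.
- **Alpha of 0.15.** It could be read as a separate error. It is an openly liberal choice in a pilot that claims no family-wise control, and the *Discussion* concedes that moderators may not be definitively evaluated. The objection stands. The concession concerns sample size, however, and does not touch the structural bias.

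**Conclusion.** The concern holds for the incident episodes and for suicidal ideation with plan or intent. As written, the interaction test would show negative moderation produced by the stopping rule: about −10, −7 or −3 points for stops at week 3, 6 or 9 under cumulative scoring, and about −7, −4 or −2 under visit-by-visit scoring. Both sets of figures assume that post-stop doses count as not taken and that the 57% and 44% planning values hold before the stop. The documents give no event rate. If events are rare, expect a biased and very imprecise estimate; an inflated false-positive rate should not be claimed.

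For drug use, alcohol and BSI the point is weaker: values from weeks 3 to 12 are post-randomisation and could respond to arm, but have no built-in link to stopping. The 56% to 80% figure assumes independence among moderators that are plainly correlated, and supports cautious wording only.

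The arm comparisons of adherence and abstinence do not rest on these interaction tests. The moderation aim does.

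**What to change.** 1. Remove incident major depressive, manic and psychotic episodes and suicidal ideation with plan or intent from the interaction tests. Report them by arm as safety outcomes and as reasons for stopping varenicline.
2. Define the remaining moderators from baseline: drug use (self-report or urine), AUDIT at the stated cut-offs, and BSI Global Severity Index T score ≥ 63. Table 1 and the alcohol and drug use section already schedule these measurements.
3. Report interaction estimates with confidence intervals, labelled exploratory, and claim no moderation merely because a p-value falls below 0.15.
4. Reconcile *Adherence measures*, *Moderating effects of drug use and psychiatric symptoms* and *Addressing varenicline risk potential* on how adherence is scored after a protocol-required stop. This concerns scoring only; the stopping rule itself is not in question.

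The cost is a change of analysis wording, with no new data collection. The downside is that the question about ongoing, post-baseline use becomes descriptive.
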